### The current trial

This paper describes the protocol for the Services for Teens Engaging in Problem Sexual Behaviour (STEPS-B) trial, a UK feasibility evaluation of MST-PSB. The MST-PSB intervention uses the term ‘problem sexual behaviour’ to describe young people who display serious non-normative sexual behaviours that victimize others, which can be aggressive or non-aggressive sexual acts [40]. Gerardin and Thibaut [41] defined this behaviour as committing any sexual act with a person of any age against the victim’s will, or in an aggressive, exploitative or threatening manner, including non-contact sexual acts such as exposing one’s genitals or masturbating in public.

The STEPS-B trial aims to assess the feasibility of implementing MST-PSB and also the barriers to implementing it: young people who display problem sexual behaviour suffer intense stigma and blame [42]. There are also well-documented challenges to effectively identifying, assessing and intervening with this clinical population in the United Kingdom [43]. As well as evaluating the effectiveness of MST-PSB in a UK context, the aim of the trial is to determine whether MST-PSB can be implemented fully and at a scale that would warrant a full trial. This feasibility trial will follow rigorous RCT guidelines, and therefore, part of the evaluation will be to determine whether a stringent RCT is realisable, as there have been no previous RCTs of interventions addressing adolescent problem sexual behaviour in the United Kingdom.

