### Aims

The aim of STEPS-B is to carry out a feasibility trial that will inform policymakers, commissioners of services and professionals about the potential for implementing MST-PSB as a programme for intervening with young people showing problem sexual behaviour. Should MST-PSB show potential in the United Kingdom context, the trial will determine what would be necessary to implement the programme more fully and at a scale that would warrant a full trial.

The trial will investigate whether MST is associated with the elimination or reduction of levels of sexual and nonsexual offending; reduction or elimination of problem sexual behaviours; reduction in nonsexual antisocial behaviour; less time spent in custodial institutions; and improved educational outcomes. It will also aim to establish the cost of MST-PSB relative to MAU, and the cost-effectiveness of providing this intensive form of intervention against the background of costs incurred in the 20-month period following randomization.

Finally, the trial will investigate specific feasibility issues that pertain to effective implementation of MST-PSB in the United Kingdom. These include: specific characteristics of young people’s problem sexual behaviour, where they are referred from, and what services have been or are being provided to them whether or not they are randomized into the trial; the beliefs and attitudes held by professionals around family intervention for this population, given that the young person will remain in the family home despite having committed sexually harmful behaviour towards other young people, including, in some cases, a sibling living in the same home; the degree to which professionals are supportive of the procedures and demands associated with an RCT research evaluation, including the randomization and its consequences; and the degree to which the institutions and agencies that manage young people showing problem sexual behaviour, such as the courts and child protection services, are able to support an RCT evaluation. It will also investigate the acceptability of the trial protocol to young people and their carers, and will gather information on their experience of MST-PSB and MAU interventions, through qualitative interviews following completion of treatment.

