### Randomization and procedures to minimize bias

Following consent and the baseline (pre-randomization) assessment, a trial identification number is assigned to the participant. Eligible consenting participants are randomized to MST-PSB or MAU on a 1:1 basis by the Trials Unit at UCL through the use of a secure randomization service that ensures allocation concealment. A computer-generated adaptive minimization algorithm that incorporates a random element is used with the following stratification factors: gender, age (10–14, 15–17), conduct problems presenting with problem sexual behaviour (yes or no) and age differential between the perpetrator and victim (<4 years or ≥4 years). These strata were selected because previous research has shown that a greater age differential between perpetrator and victim, and whether the young person is also displaying antisocial behaviour, are associated with more severe maladjustment and poorer long-term outcomes [6, 47, 48].

To minimize the possibility that RAs will learn of the treatment allocation for any individual participant, the RAs are blind to treatment allocation at randomization, and there is no direct communication between RAs and therapists. This procedure has been used in the START trial of standard MST [28] and has proven to be effective.

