### Primary outcome

The primary outcome of the proportion of cases where a sexual offence has been incurred during the follow-up period will be described by a Kaplan-Meier graph and summarized by the proportions in each group with a new sexual offence by 20 months. The linked outcome of out-of-home placement will also be described by a Kaplan-Meier graph and summarized by the proportions in each group with out-of-home placement by 20 months. The number of events will be estimated in order to inform power calculations for a fully powered efficacy trial.

For time-to-event offending outcomes, the event rate will be estimated. For continuous secondary outcomes, such as questionnaire data, linear mixed effects models will be fitted in order to estimate the individual-level residual variance.

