## Discussion

There is very little research that has evaluated therapeutic interventions for young people displaying problem sexual behaviour, and to date, no RCTs have been conducted in the United Kingdom. Although the results from two RCTs of MST-PSB [18, 32] have demonstrated the success of this intervention in reducing adolescent problem sexual behaviour in the United States, the evaluation of MST-PSB and adolescent problem sexual behaviour is still in its infancy. The STEPS-B trial aims to assess the feasibility of implementation of MST-PSB in the United Kingdom. The investigators hope that the feasibility trial will determine whether MST-PSB can be implemented fully and at a scale that would warrant a full trial. In addition, in following rigorous RCT guidelines, the trial will also assess whether the implementation of a stringent RCT evaluation of adolescent problem sexual behaviour is possible. Finally, this study will be the first RCT of MST-PSB that has not been conducted by the developers of the intervention. As such, it will provide a robust test of the effectiveness of this promising intervention as well as its transportability to outside the United States.

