The research is being conducted by a team based at UCL, with data collection from cases referred to the Brandon Centre. MST-PSB aims to reduce levels of both sexual and non-sexual offending in the target population, and so offending will be used as a key measure to determine whether the intervention is effective. In addition, as out-of-home placement (whether this constitutes incarceration, hospitalization, residential schooling or local authority care) represents an unhelpful outcome for antisocial adolescents in the majority of cases, the investigators have chosen to use preservation of the family (that is, the *absence* of out-of-home placement) as the main measure of potential benefit. Other possible benefits of MST-PSB will also be examined, such as the impact on the young person’s mental health and well-being, and that of the carer(s).

To address factors associated with improvement, the investigators have taken considerable effort to monitor the effect of MST-PSB on parenting and family functioning. It is anticipated that improvement observed in association with MST-PSB will be commensurate with the impact that the intervention has on variables within the family, and for other clinically critical outcomes (for example, antisocial peer group affiliation), to be in line with changes in the purported mediating processes [46].

To assess what the benefits of MST-PSB and MAU might be, care will be taken to gather accurate descriptions of the interventions delivered to both groups in the study. In addition, the investigators will attempt to chart the subjective experience of all stakeholders in the project (that is, participants, their carers and providers and commissioners of services). The data from the trial will be analysed to determine whether the expected benefit of MST-PSB is achieved and will provide initial data on whether MST-PSB represents an economically viable option for intervening with young people displaying problem sexual behaviour.

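### The article promises a test of effectiveness, but its analysis section plans no between-arm estimate or interval, and 40 per arm could not support such a test for sexual offending

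*Protocol article*

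**What the plan says.** **Statements of purpose.** The current trial section sets an effectiveness objective beside the feasibility one: "As well as evaluating the effectiveness of MST-PSB in a UK context". The Aims state that "The trial will investigate whether MST is associated with the elimination or reduction of levels of sexual and nonsexual offending". The Discussion goes further. Of the study it says that "it will provide a robust test of the effectiveness of this promising intervention", and later that "The data from the trial will be analysed to determine whether the expected benefit of MST-PSB is achieved". The Discussion's paragraph on the primary aim also expects evidence on whether providing MST-PSB could lower out-of-home placement.

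**Sample size.** The section on sample size and power calculation gives 56 participants in two groups for 80% power at an effect size of 0.32. The Participants section plans 80, half to each arm.

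**Analysis.** Under the statistical analysis plan, the primary outcome is shown as a Kaplan-Meier graph and "summarized by the proportions in each group with a new sexual offence by 20 months". The linked outcome is likewise "summarized by the proportions in each group with out-of-home placement by 20 months". Event numbers are to inform the power calculation of a later efficacy trial. Time-to-event offending outcomes yield an event rate. For continuous outcomes, "linear mixed effects models will be fitted in order to estimate the individual-level residual variance". The only other regression, under secondary outcomes, is a logistic model of factors related to recruitment into the trial.

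**The concern.** The stated purposes and the stated analyses do not match. Each quantitative output in the analysis section either describes one arm or feeds the planning of a later trial. None contrasts the arms, and none carries an interval. Yet the Discussion says the data will settle whether the expected benefit was achieved, and the sample size rests on a two-group effect that no listed analysis estimates.

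Two things are at stake. First, the trial cannot answer a question it sets itself with the outputs it lists. Second, two bare proportions from 40 participants each give no sign of how imprecise their difference is. A reader who has been told to expect a robust test could then give a chance difference, or a chance absence of one, more weight than it deserves.

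**Working it through.** **1. The plan's own power figure.** The article states no significance level or sidedness, so 5% is assumed and 56 is read as the total.

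- Chi-square, 1 df, w = 0.32, two-sided: N = ((1.960 + 0.842)/0.32)² = 76.6, so 77.
- The same, one-sided: ((1.645 + 0.842)/0.32)² = 60.4, so 61.
- As a correlation turned into a standardised mean difference: d = 2 × 0.32/√(1 − 0.32²) = 0.676. This needs 70 in total two-sided and 56 one-sided.

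So 56 is reproduced by a one-sided 5% calculation that treats 0.32 as a correlation. Under the two-sided chi-square test, 56 gives 67% power and the planned 80 gives 82%. On any of these readings the figure is the power of a between-arm test, and the analysis section contains none.

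**2. Claims against outputs.**

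| Output in the analysis section | Purpose given | Contrasts the arms? |
|---|---|---|
| Kaplan-Meier graph and proportion per arm, sexual offence | description | no |
| Kaplan-Meier graph and proportion per arm, placement | description | no |
| Number of events | power of a later trial | no |
| Event rate | none given | no |
| Mixed models, questionnaires | residual variance | not stated |
| Logistic regression | predictors of recruitment | no |

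**3. What an interval would show.** Inputs: 40 per arm (Participants section), and sexual reconviction of 5 to 14% (Background), assumed equal in both arms. Wald half-width = 1.96 × √(2p(1 − p)/40).

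- p = 0.05: 1.96 × √(0.095/40) = 0.096, or 9.6 points; 2.0 expected events per arm.
- p = 0.10: 1.96 × √(0.180/40) = 0.131, or 13.1 points; 4.0 events per arm.
- p = 0.14: 1.96 × √(0.2408/40) = 0.152, or 15.2 points; 5.6 events per arm.

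Each half-width exceeds the rate it belongs to. The article gives no expected placement rate. The widest case, p = 0.50, is 1.96 × √(0.50/40) = 0.219, or 21.9 points.

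**4. Power on the same assumptions.** Two-sided 5%, normal approximation: Φ((δ − 1.96 × SE₀)/SE₁), where SE₀ is pooled and SE₁ unpooled. A halving is detected with 8% power from 5%, 13% from 10% and 17% from 14%. For 14% against 7%: SE₀ = √(2 × 0.105 × 0.895/40) = 0.0685, SE₁ = √((0.1204 + 0.0651)/40) = 0.0681, and Φ((0.07 − 0.1344)/0.0681) = 0.17. Even a fall from 14% to zero gives about 70%.

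**5. Why the 82% does not carry over.** With equal arms the effect size is (p₁ − p₂)/(2√(p̄(1 − p̄))). For 14% against zero it is 0.14/(2√(0.07 × 0.93)) = 0.27. If the control rate is 14% or less, a reduction cannot reach the powered effect of 0.32 on sexual offending.

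**The case against.** The strongest reply is that this is a feasibility trial and is called one throughout. Curves, per-arm proportions and planning quantities are a coherent analysis for that purpose, and a journal article may leave the rest to a full analysis plan that is not shown. Much of this stands. A descriptive analysis is legitimate, and the Discussion's sentence about placement is softer than its others. What does not fall away is the conflict inside the article. It has its own statistical analysis plan and gives purposes for the main quantities there, and those purposes differ from the conclusions it announces. A fuller plan that follows the section cannot meet the claims, and one that meets the claims departs from the section.

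Three stronger readings are tempting and are not supported.

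- A reader might infer that a full trial sized on the residual variance would be too small. The term is ambiguous, the article does not say a later trial would be sized on it, and the power-calculation purpose is attached to event numbers. A repeated-measures model with a person-level random effect would also yield the between-person variance.
- A reader might fault the absence of the minimization factors, which include "conduct problems presenting with problem sexual behaviour (yes or no) and age differential between the perpetrator and victim". Covariate choice is commonly left to a full analysis plan. Two to six events per arm would hardly bear adjustment for four factors.
- A reader might infer that effectiveness will be judged by comparing two proportions by eye. The article states no decision rule of any kind. The mixed models may well contain an arm term, but no arm difference is named as an output.

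**Conclusion.** The point holds as a mismatch between claims and analysis. The effectiveness statements in The current trial section and the Discussion, together with the two-group power calculation, call for a between-arm result that the analysis section does not plan.

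For sexual offending the half-width of the 95% interval is about 10 to 15 points at 40 per arm. This rests on three assumptions: the background reconviction range applies to new sexual offences within 20 months, both arms share the rate, and all 80 are followed up. The Wald formula is rough at so few events. If offences recorded in this trial are more common than reconvictions, the interval is wider in points but narrower relative to the rate. The mismatch itself depends on none of these figures. They show only that adding the comparison would not make the trial a robust test on this outcome, so the wording must change as well.

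**What to change.** 1. In the primary outcome part of the statistical analysis plan, add the between-arm difference in proportions by 20 months, with a 95% confidence interval, separately for new sexual offence and for out-of-home placement. Leave both unadjusted, given the few events expected, and use an interval method suited to small counts.
2. For questionnaire outcomes, report the arm difference with a 95% confidence interval from the mixed models already planned, adjusted for the baseline score. Keep the residual variance as a further output.
3. In The current trial section and in the Discussion, including the paragraph on the primary aim, reword the statements about testing effectiveness and determining benefit. Suitable wording would be that the trial gives preliminary estimates, with confidence intervals, to inform a full trial.

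The cost is a few sentences and a few extra lines of output. Table 1 already schedules the police and social care records and the month 0 questionnaires, so no participant, visit or measure is added.

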### Secondary outcomes

The feasibility outcome evaluating individual and systemic factors associated with recruitment into the trial will be analysed using logistic regression. The total score and subscale scores on the Feasibility Questionnaire will undergo descriptive analyses to characterize the direction and range of attitudes by referrers involved in the MST-PSB trial. As noted above, qualitative interviews eliciting the views of young people and their carer(s) on the underlying principles and demands of participating in an RCT will be analysed using IPA.

## Discussion

There is very little research that has evaluated therapeutic interventions for young people displaying problem sexual behaviour, and to date, no RCTs have been conducted in the United Kingdom. Although the results from two RCTs of MST-PSB [18, 32] have demonstrated the success of this intervention in reducing adolescent problem sexual behaviour in the United States, the evaluation of MST-PSB and adolescent problem sexual behaviour is still in its infancy. The STEPS-B trial aims to assess the feasibility of implementation of MST-PSB in the United Kingdom. The investigators hope that the feasibility trial will determine whether MST-PSB can be implemented fully and at a scale that would warrant a full trial. In addition, in following rigorous RCT guidelines, the trial will also assess whether the implementation of a stringent RCT evaluation of adolescent problem sexual behaviour is possible. Finally, this study will be the first RCT of MST-PSB that has not been conducted by the developers of the intervention. As such, it will provide a robust test of the effectiveness of this promising intervention as well as its transportability to outside the United States.

Evidence to support MST-PSB remains limited. Both prior evaluations of MST-PSB were conducted in the United States by the developers of the intervention and recruited participants solely through the juvenile court system. Moreover, in one of these two trials, measures of critical sexual and non-sexual reoffending outcomes were not reported and, as noted by the authors, the sample of young sexual offenders displayed very low levels of general psychopathology [32]. This finding appears to run contrary to knowledge that young people displaying problematic sexual behaviour have significant difficulties in other areas of their lives [8–10]. Consequently, while the evidence from the United States suggests that MST-PSB is a promising treatment when participants are recruited through the court system and when the intervention involves the developers of the programme, the question of whether MST-PSB is effective in reducing problem sexual behaviour in adolescents requires further research [17]. Furthermore, its potential applicability to the United Kingdom has yet to be tested. Moreover, the provision for adolescents who display problem sexual behaviour in the United Kingdom is difficult to compare with that in the previous evaluations, and the degree to which samples recruited into trials in the United Kingdom and the United States will be similar is unknown. It is clear that further high-quality RCTs with minimal involvement of the developers and long-term follow-up in the community are required to identify effective interventions for adolescent problem sexual behaviour and specifically to test the effectiveness of MST-PSB.

The primary aim of this study is therefore to conduct a rigorous, community-based trial in which MST-PSB is compared with the range of services that are typically provided to adolescent sexual offenders in the United Kingdom (that is, MAU). Whereas there is no good evidence that MAU for these young people and their families works, there is some evidence available to suggest that MST-PSB is of benefit. Therefore, this evaluation of both treatment options will enable closer observations of MAU services to provide an evaluation of interventions currently available in the localities, as well as MST-PSB. This pragmatic trial will inform policymakers, commissioners of services and professionals about the potential of MST-PSB in the UK context. Specifically, it will provide evidence to determine whether the provision of MST-PSB could reduce the incidence of out-of-home placements for young people at risk of being removed from their homes primarily because of problem sexual behaviour.

To ensure that the study achieves the fairest and least biased assessment of the potential benefits of MST-PSB, the investigators have designed the study with the support of MST Services but will carry out the RCT independently from the developers; however, the developers provide regular consultation to the clinical service at the Brandon Centre to ensure that MST-PSB is delivered to the highest levels of fidelity. As part of the feasibility evaluation, individual and systemic factors will be assessed that may be associated with young people being recruited into the trial, the beliefs and attitudes held by practitioners about the usefulness of empirically evaluating services for problematic sexual behaviour in the United Kingdom, and the perceptions of young people and their carers of having participated in an RCT for problematic sexual behaviour and of the intervention that they received.

The research is being conducted by a team based at UCL, with data collection from cases referred to the Brandon Centre. MST-PSB aims to reduce levels of both sexual and non-sexual offending in the target population, and so offending will be used as a key measure to determine whether the intervention is effective. In addition, as out-of-home placement (whether this constitutes incarceration, hospitalization, residential schooling or local authority care) represents an unhelpful outcome for antisocial adolescents in the majority of cases, the investigators have chosen to use preservation of the family (that is, the *absence* of out-of-home placement) as the main measure of potential benefit. Other possible benefits of MST-PSB will also be examined, such as the impact on the young person’s mental health and well-being, and that of the carer(s).

To address factors associated with improvement, the investigators have taken considerable effort to monitor the effect of MST-PSB on parenting and family functioning. It is anticipated that improvement observed in association with MST-PSB will be commensurate with the impact that the intervention has on variables within the family, and for other clinically critical outcomes (for example, antisocial peer group affiliation), to be in line with changes in the purported mediating processes [46].

To assess what the benefits of MST-PSB and MAU might be, care will be taken to gather accurate descriptions of the interventions delivered to both groups in the study. In addition, the investigators will attempt to chart the subjective experience of all stakeholders in the project (that is, participants, their carers and providers and commissioners of services). The data from the trial will be analysed to determine whether the expected benefit of MST-PSB is achieved and will provide initial data on whether MST-PSB represents an economically viable option for intervening with young people displaying problem sexual behaviour.

We anticipate that the trial will also have positive effects on practice with this group of young people, irrespective of the trial outcomes. As noted, there is a lack of coherence within and across the systems that manage these young people; there are challenges to effectively identifying, assessing and intervening with this clinical population; and there has been very limited development of evidence-based interventions [43]. As we develop relationships with the referrers and clinical services devoted to working with this population, we will help them to develop pathways for identifying and assessing problematic sexual behaviour in terms of criteria that are evidence-based, and will encourage them to identify credible interventions that respond to clearly defined needs and that will function as suitable comparators to MST-PSB. This feasibility trial, while specifically evaluating MST-PSB versus the MAU typically available for young people showing problematic sexual behaviour, is consistent with UK government policy that strongly advocates and funds evidence-based practice for children and young people [79, 79].

Finally, the qualitative aspects of the study, which will elicit the views of this stigmatized and marginalized group of young people, will provide valuable information about their lived experiences as sexual offenders, while the assessment of practitioners’ views specifically regarding provision of family and evidence-based treatments for this population will help us to understand the mental health context within which evidence-based services will need to develop. The qualitative data will complement the quantitative results about the treatment effectiveness of both MST-PSB and currently available services to enrich our understanding of the strengths and challenges facing mental health services for young sexual offenders in the United Kingdom.

